## Abstract

**Background::**

Cerebral palsy is 1 of the diseases critically affecting the health of children. The spasmodic type is the most common, characterized by the increased muscular tension. It often leads to lifelong disability, bringing a heavy economic burden to families and society. As a key treatment in traditional Chinese medicine, pediatric massage has a significant clinical effect on cerebral palsy in children; however, high-quality randomized controlled studies are lacking. The main objective of this study was to evaluate the efficacy of pediatric massage for children with spastic cerebral palsy.

**Methods/Design::**

The study will be a multicenter, single-blinded, randomized-controlled pilot trial. During the period from June 2019 to December 2020, 182 children with spastic cerebral palsy will be randomly divided into experimental and control groups in a 1:1 ratio. The experimental group will undergo the modified selective spinal massage method combined with the basic rehabilitation treatment, while only the basic rehabilitation treatment would be performed for the control group. The intervention period of the study will last 12 weeks, 5 days weekly on weekdays. The primary outcomes include a modified Ashworth scale assessment and gross motor function test. The secondary outcomes include the 4-diagnostic scale of Chinese medicine and children's intelligence. The observation index will be measured during the complete 12 weeks duration after the treatment of the child, that is, before treatment, after 4 weeks of treatment, after 8 weeks, and after 12 weeks of treatment.

**Discussion::**

This study aims to evaluate the efficacy of pediatric massage on children with spastic cerebral palsy; if the outcome is positive, it can provide a reference for the further promotion and application of pediatric massage in the treatment of spastic cerebral palsy.

**Trial registration::**

Chinese ClinicalTrials.gov, ID: ChiCTR1900021666. Acupuncture-Moxibustion Clinical Trial Registry, AMCTR: (AMCTR-IPR-19000260) Registered on 04 March 2019.

## Introduction

1

Cerebral palsy describes a set of permanent diseases that develop in motion and posture, leading to limited activity, owing to the occurrence of non-progressive disorders in the developing fetuses or the baby's brain. The dyskinesia of cerebral palsy is usually accompanied by disturbances in perception, cognition, communication, behavior, epilepsy, and secondary musculoskeletal problems.^[1]^ Cerebral palsy is 1 of the major diseases causing disability in children. Currently, the prevalence rate of cerebral palsy is approximately 1.5% to 4% worldwide and 2.48% in China, among which the spastic type is the most common, accounting for about 60%.^[2,3]^ It is mainly characterized by increased muscle tension. Studies have shown that the most common type of cerebral palsy in premature infants is spastic diplegia, accounting for 52.7%.^[4]^ The disease with a high incidence is harmful and is 1 of the important reasons for harming the health of children. It often leads to permanent disability, seriously affects the quality of life and mental health of children, and brings a heavy economic burden to families and society.

Currently, there is no specific medication for the treatment of spastic cerebral palsy. The most commonly used are anti-muscular tension drugs. Most of the anti-spasmodic drugs, including benzodiazepines and baclofen, can be used in combination, which can reduce muscle tension, relieve spasm, and improve function. However, side effects such as ataxia, constipation, drowsiness, and dependence commonly occur in clinical practice.^[5]^ Although botulinum toxin can relieve the spasm quickly, its effect is short-lasting and requires repeated treatment, which aggravates the financial burden on the patient's family.^[6]^ Non-drug therapy mainly includes surgical treatment and rehabilitation training. Selective posterior rhizotomy of the spinal nerve is a newer surgical method for the treatment of spasmodic cerebral palsy and is effective in alleviating spasmodic state.^[7]^ However, there are certain requirements for patients. The optimal age of operation is 2 to 6 years, and it is appropriate only for patients with spastic cerebral palsy, close to normal intelligence, with muscle tension above grade 3, and maintaining certain muscle strength and motor function.^[8]^ Patients with hand-foot-crawling and ataxia types of cerebral palsy are not suitable for this operation. Postoperative rehabilitation training is a fundamental requirement for successful treatment. Surgery also causes trauma, and a high recurrence rate is observed during follow-up; therefore, the choice of surgical treatment should be carefully considered.^[9]^ Rehabilitation training is the most widely used treatment for cerebral palsy. The common rehabilitation methods include physical therapy, occupational therapy, exercise therapy, speech training, sensory training, and guided education.

The pediatric massage is based on the basic theory of Traditional Chinese Medicine, the practices on the meridian and acupoints, giving the body a benign physical stimulation, making the function of zang-fu organs blood of equilibrium state and is economical, convenient, and safe. It has the advantages of easy acceptance for improving cerebral palsy. Clinical studies^[10–12]^ have shown that massage is effective in the motor development, sleep quality and learning, and memory effects of cerebral palsy. The evidence for most of these interventions is weak, partly owing to the lack of randomized controlled trials; however, also because of the many confounding factors of treatment, such as the effects of comorbidities. Therefore, we propose that massage therapy can improve the functional recovery of children and help in designing the randomized controlled trials to further improve the relevant evidence.

## Methods

2

### Study design

2.1

The proposed study will be a multicenter, single-blinded, randomized controlled pilot trial. The trial will be commenced after ethical approval has been obtained from the second affiliated hospital of the Yunnan University of Chinese Medicine. The clinical trial will be conducted in the Yunnan rehabilitation center for the disabled, Kunming children's hospital, the second affiliated hospital of the Yunnan University of traditional Chinese medicine, and Yuxi Hospital of Traditional Chinese medicine. All study-related procedures will be performed after obtaining written informed consent from the participants. The clinical trial is designed and reported following the Consolidated Standards of Reporting Trials guidelines.

### Participants

2.2

#### Sample size estimation

2.2.1

The estimated sample size will be compared using 2 sets of odds ratios. The formula is as follows:$$n_{1}={\left[\frac{z_{1}-\alpha /2\sqrt{\bar{p}\bar{q}(1+1/r)}+z_{1}-\beta \sqrt{p_{1}q_{1}+p_{2}q_{2}/r}}{\Delta }\right]}^{2}=82$$

A total of 182 children were calculated using the transcript estimation method for the robustness of the clinical trial. The specific index is that α = 0.05 on both sides of the tail, and (1-β) is 0.80, and the absolute difference of the comprehensive result variable index is 20%. Our initial estimate of the sample size is 82, and the loss rate is increased by 10%, and 91 is determined for each group. Thus, the 2 groups totaled 182.^[13,14]^

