### Randomization and blinding

2.4

The staff member will refer to a specific random number handbook generated by an independent statistician based on statistical software before study activation to determine the study intervention assigned to the randomized patient. The randomization schedule is layered by the position of each 4-bit variable block. Participants will be randomly assigned to 1 of the 2 groups in a 1:1 ratio after completion of baseline assessment, according to a randomized block list generated by an independent research assistant using R, and the code will be kept in opaque sequentially numbered envelopes. The treatment allocation codes will be enclosed by an independent research assistant in sequentially numbered opaque envelopes and will not be revealed until the participants have completed all baseline assessments and immediately before the first massage treatment. The single-blind method is adopted in this study, and there are two-level blind methods. First, blind evaluation, in which the participants are evaluated by a third party who does not know the grouping. Second, the blind statistical analysis, where the statistical data will be analyzed by statisticians with unclear grouping and its meaning. (Fig. 1)

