### Primary outcome measure

2.7

1.Modified Ashworth ScaleOwing to the presence of sputum, quadriplegia, and hemiplegia, the lower limb muscle tone (triceps, soleus, gastrocnemius) will be assessed using a modified Ashworth scale.^[19,20]^ It includes 6 rating levels, 0, 1, 1+, 2, 3, and 4. For statistical convenience, 0, 1, 1+, 2, 3, and 4 levels of the muscle tension level in the scale will be determined to be 1, 2, 3, 4, 5, and 6 points, respectively. All subjects are guaranteed not to be treated with any muscle relaxants. During the evaluation, efforts should be made to avoid position metastasis, skin irritation, low ambient temperature, emotional agitation, pain, urinary tract infection, or urination before the examination. If there is a clonic or transient paroxysmal contraction, test again after the disappearance.2.Gross motor function rating scale (GMFM)

The gross motor function score will be evaluated using the GMFM for gross motor function evaluation. GMFM currently has 88 versions (GMFM-88) and 66 items (GMFM-66).^[21]^ GMFM-88 is a sequential scale, each using a 4-level scoring method, divided into 5 functional areas: Area A (lying position and turning over), a total of 51 points (17 items); Area B (sitting), total score 60 points (20 items); Area C (crawling and squatting), total score of 42 points (14 items); Area D (station), total score 39 points (13 items); Area E (walking, running and jumping). The total score is 72 points (24 items). The evaluation results include 5 functional distinction values and total scores expressing the corresponding energy regions and overall gross exercise capacity, respectively. The Chinese translation is based on the 1993 GMFM revision. Evaluate 3 designated physicians or therapists to perform in a quiet, independent, well-lit room. The room temperature will be controlled at 20°C to 30°C, and the children's clothes will be 1 to 2 layered. In the absence of a violation of the assessment requirements, the same family members should be present in each assessment to encourage the child to perform at an optimal level.

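### The 80% power is stated for an undefined binary comprehensive rate, so it applies to neither declared primary outcome (MAS or GMFM score)

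*Protocol article*

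**What the plan says.** **Sample size (protocol article, 2.2.1).** The calculation is introduced with "The estimated sample size will be compared using 2 sets of odds ratios". The printed formula uses p1, q1, p2, q2 and their pooled values, so it compares two proportions. The inputs are "α = 0.05 on both sides of the tail", power 0.80, and the premise that "the absolute difference of the comprehensive result variable index is 20"%. The two rates themselves are not given. The result is carried forward as "Our initial estimate of the sample size is 82, and the loss rate is increased by 10%, and 91 is determined for each group", and then "Thus, the 2 groups totaled 182".

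**Outcomes (Abstract, 2.7, 2.8).** The Abstract says "The primary outcomes include a modified Ashworth scale assessment and gross motor function test". Section 2.7 recodes the six MAS grades as 1 to 6 points. For the other primary it says "The gross motor function score will be evaluated using the GMFM for gross motor function evaluation", and reports five domain values and a total. Neither scale is given a responder threshold. The secondary outcomes in 2.8 are the Bayley intelligence scale and a traditional Chinese medicine score with a maximum of 54 points. Neither is a rate.

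**Analysis (2.12).** The main analysis is a chi-square test of a comprehensive rate, which is not defined there either. The same section also plans t-tests between groups, paired t-tests within groups and repeated-measures analysis of variance, which are methods for scores.

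**The concern.** A power statement holds only for the variable, effect and variability that went into it. Here the variable is a binary index that appears in the sample-size paragraph and, in similar words, in the analysis section, but never in the outcome sections. No mean difference or standard deviation for MAS or GMFM enters the calculation. The 80% therefore cannot be carried over to the outcomes on which the trial says it will be judged.

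Two things are at stake. First, readers will take 80% as the trial's power on its primaries, while the effect that the design can detect on those scales is not stated. Second, the article offers two candidates for its main result: an undefined rate (2.2.1, 2.12) and two scores (Abstract, 2.7). As the article stands, neither the definition of the rate nor the choice between the candidates is fixed.

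**Working it through.** **Inputs from the document.** Two-sided alpha 0.05 (z = 1.960), power 0.80 (z = 0.842), difference 0.20, and loss 10% (all from 2.2.1). Allocation is equal, so r = 1: "Participants will be randomly assigned to 1 of the 2 groups in a 1:1 ratio" (2.4). The rates p1 and p2 are not stated, so they are scanned.

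**Step 1: the plan's own figure.** With r = 1 the printed formula is

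n = [1.960 × √(2·p̄·q̄) + 0.842 × √(p1·q1 + p2·q2)]² / 0.20²

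At an assumed 60% v 80%: p̄·q̄ = 0.70 × 0.30 = 0.21, and p1·q1 + p2·q2 = 0.24 + 0.16 = 0.40. So n = [1.960 × 0.648 + 0.842 × 0.632]² / 0.04 = 81.2, rounded up to **82**. By symmetry 20% v 40% gives the same. Power at 82 per group is then 80.4%.

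Other pairs that differ by 20 points:

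| Assumed rates | n per group |
|---|---|
| 5% v 25%, or 75% v 95% | 49 |
| 10% v 30%, or 70% v 90% | 62 |
| 20% v 40%, or 60% v 80% | 82 |
| 30% v 50%, or 50% v 70% | 93 |
| 40% v 60% | 97 |

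The printed inputs alone do not fix 82, but 82 is what the formula returns at two plausible pairs of rates.

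**Step 2: allowance for loss.** 82 × 1.1 = 90.2, rounded up to 91; 82 / 0.9 = 91.1. The stated 91 is within rounding on either reading, and 2 × 91 = 182. There is no issue here.

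**Step 3: is the powered variable a declared outcome?** The variable in 2.2.1 is a binary comprehensive index. The primaries in 2.7 are a 1 to 6 grade and GMFM scores, and the secondaries in 2.8 are two further scores. The only counterpart is the rate in 2.12, which has no definition and no stated link to MAS or GMFM.

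**Step 4: what 82 per group delivers on a score.** The document gives no target difference or standard deviation, so the effect is in standard deviation (SD) units and is assumed. For an unadjusted two-sample t-test, normal approximation, two-sided 0.05:

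Detectable difference = (1.960 + 0.842) × √(2/82) = 2.802 × 0.156 = **0.44 SD** at 80% power (also 0.44 by the non-central t).

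Power at d = Φ(d × √(82/2) − 1.960), with √41 = 6.403:

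| Assumed d | Power, 82 per group | Power, 91 per group (no loss) |
|---|---|---|
| 0.20 | 25% | 27% |
| 0.30 | 48% | 53% |
| 0.40 | 73% | 77% |
| 0.50 | 89% | 92% |
| 0.60 | 97% | 98% |

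For the six-level ordinal MAS these figures are approximate.

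**The case against.** The strongest reply is that the rate is not foreign to the plan. Section 2.12 names a comprehensive rate and makes its chi-square test the main analysis, which fits the formula in 2.2.1. This stands, and it limits the point: one cannot say that the trial does not analyse such a rate. It does not remove the mismatch, because the rate is neither defined nor listed as an outcome, while two scores are declared primary.

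A second reply is that this is a condensed article, so the two rates may be given in the full protocol. That also stands. The missing rates are therefore not the defect, and the range of 49 to 97 shows only that 82 rests on unprinted rates. Condensation does not explain why the powered variable and the declared primaries differ, since both are printed here.

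The article calls the trial a pilot. That would carry weight if no power were claimed, but 2.2.1 makes a formal 80% claim and the Abstract gives efficacy as the main objective.

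Some stronger readings are tempting but not supported:

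- **The 82 is miscalculated.** It is reproduced at 60% v 80% or 20% v 40%.
- **The trial is underpowered.** Power on MAS and GMFM is unstated, not shown to be low; at an assumed 0.50 SD it is 89%.
- **A null result on MAS or GMFM would be uninterpretable.** A confidence interval on either scale can be read whatever the planning assumption was.
- **Alpha should have been split between two primaries.** The article does not say whether success needs both or either, and this is commonly settled in the analysis plan.

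**Conclusion.** The point holds as a mismatch between sample size and endpoint. The 80% power in 2.2.1 belongs to an undefined binary rate and to neither declared primary outcome. Section 2.12 repeats the conflict by making that rate the main analysis.

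Its size can be given only conditionally. With 82 evaluable per group, 80% power on a score requires a true standardised difference of about 0.44. Power is about 48% if the difference is 0.30 and 89% if it is 0.50. This assumes an unadjusted t-test at two-sided 0.05 and effect sizes that the document does not supply, and it is approximate for MAS. The total of 182 is not challenged.

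**What to change.** Keep 182 children and change sections 2.2.1, 2.7 and 2.12 together, so that one main variable runs through all three.

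**Preferred.**

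- In 2.2.1, replace the 20% claim with what the design delivers on the declared primaries: 82 evaluable per group give 80% power at two-sided 0.05 for a standardised difference of about 0.44 (unadjusted t-test, approximate for MAS), about 48% at 0.30 and 89% at 0.50.
- Name the GMFM score (total or a domain) and the time point (4, 8 or 12 weeks) to which this refers. That choice is the sponsor's.
- In 2.12, make the between-group comparison of those scores the main analysis.
- If a responder rate is kept, define it in advance and list it as secondary.

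**Alternative.** If the comprehensive rate is the intended primary outcome, list and define it as such in 2.7 and the Abstract, and state in 2.2.1 the two rates behind 82. Section 2.12 can then keep the chi-square test as the main analysis.

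**Cost.** A rewritten sample-size paragraph and matching edits to the outcome and analysis sections, with no extra children. The downside of the preferred route is that the stated power becomes conditional on an assumed standardised difference.

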### Subject recruitment

2.3

Inclusion criteria:

(1)Aged 1 to 3 years, both male and female children.(2)Grading of the large motor function at the I-III level.^[15,16]^(3)Children who meet the diagnostic criteria for spastic cerebral palsy.^[17]^(4)Muscle tone between I-IV (according to the newly revised Ashworth scale).(5)Follow the doctor advice during the study and insist on receiving the tester.

Exclusion criteria:

(1)Those with severe mental illness and severe epilepsy.(2)Organized diseases involving other organs such as the heart, liver, and kidney.(3)Exclusion of leukodystrophy, infantile spinal muscular atrophy, spin cerebellar ataxia, genetic metabolic diseases such as phenylketonuria, congenital cretinism, and congenital hydrocephalus.(4)Failure to meet the inclusion criteria, failure to complete the test according to the regulations, and the treatment of patients who have an influence on the test results during the study, the incomplete data affect the clinical efficacy observation.(5)Spontaneous bleeding tendency.

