### Reasons for withdrawal

2.10

When a participant withdraws before completing the study, the reasons for withdrawal will be recorded.

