### Statistical analyses^[25]^

2.12

The primary analysis will be performed using intention-to-treat methods and therefore include all randomized child data. All data will be checked into the double machine using Epidata 3.1 software for database management.

Specific statistical analysis methods: The baseline characteristics of patients in the 2 groups will be reported using frequency distribution and descriptive statistics (including measurements of concentration trends and dispersion). The main analysis of the comprehensive measurement of the rate of counting data will be the chi-square test. Two independent samples of the *t*-test will be performed between the 2 groups. The paired t-test will be used to compare the outcome variables of each treatment group before and after the treatment. The difference between the multiple measurements of the same group will be conducted using the multiple measures data analysis of variance, combined with logistic regression analysis to examine the adjustment effect of clinically relevant covariates, which will be the results (gender, birth weight, gestational age). We will also follow the pre-specified subgroup analysis. All analyses will be performed using the R software. The aforementioned steps will be monitored by the third-party tests, and the quality control of the test will be carried out. The blind law is unified and responsible.

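### Exclusion criterion 4 removes children for events after randomisation, which contradicts the intention-to-treat primary analysis and can bias the comparison

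*Protocol article*

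**What the plan says.** **Section 2.3, exclusion criterion 4** has four parts. The first, not meeting the inclusion criteria, can be checked at screening. The others are:

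- "failure to complete the test according to the regulations"
- "the treatment of patients who have an influence on the test results during the study"
- "the incomplete data affect the clinical efficacy observation"

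**Section 2.3, inclusion criterion 5** also looks ahead: "Follow the doctor advice during the study and insist on receiving the tester".

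**Section 2.4** fixes the timing: "Participants will be randomly assigned to 1 of the 2 groups in a 1:1 ratio after completion of baseline assessment". Allocation stays concealed until immediately before the first massage treatment.

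**Section 2.12** sets the analysis population: "The primary analysis will be performed using intention-to-treat methods and therefore include all randomized child data".

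**Section 2.10** says of early leavers only this: "When a participant withdraws before completing the study, the reasons for withdrawal will be recorded".

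**The concern.** Eligibility criteria should describe children as they are before randomisation. Three parts of criterion 4 describe what happens afterwards: whether the child finishes, whether other treatment is given, and whether the data are complete. Inclusion criterion 5 can add a fourth route, because criterion 4 also excludes anyone who fails an inclusion criterion.

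Randomisation protects the comparison only while all randomised children stay in it. Here there are reasons to expect removal to differ by arm. Only the experimental group receives the added massage. The blinding in section 2.4 covers the assessor and the statistician, not the families or the therapists. Section 2.5 lets basic rehabilitation follow each hospital's concept or the cost bearers' demands, so other treatment can vary between children. Families who see little progress may stop or look elsewhere. Removing those children would leave the better responders in whichever arm loses them.

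**Working it through.** **1. Timing of each exclusion ground**

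| Ground in criterion 4 | When it can be known | Compatible with section 2.12? |
|---|---|---|
| Inclusion criteria not met | Screening (except inclusion 5) | Yes |
| Trial not completed | After randomisation | No |
| Influential treatment during the study | After randomisation | No |
| Incomplete data affecting efficacy | After randomisation | No |

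Nothing in the article restricts the last three rows to screening or to a per-protocol set, or says that section 2.12 overrides them.

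**2. The plan's own figures (section 2.2.1)**

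82 per group plus 10%: 82 × 1.10 = 90.2, rounded up to 91; 2 × 91 = 182. This reproduces. The response rates behind 82 are not given. A pooled two-proportion formula (two-sided 0.05, power 0.80, difference 0.20) returns 82 for 0.60 v 0.80 or for 0.20 v 0.40. The 10% allowance replaces lost numbers. It does not correct selective loss.

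**3. Difference in treatment load**

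The abstract states: "The intervention period of the study will last 12 weeks, 5 days weekly on weekdays". That is 12 × 5 = 60 massage sessions, in the experimental group only.

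**4. Illustration with a continuous outcome** (removal rates and correlations are assumptions)

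Inputs: no true effect, 91 per arm, normal outcome, two-sample t-test at 0.05. In the massage arm, a fraction *q* is removed on a normal score that correlates *r* with poor outcome. Control removal is random.

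Bias in SD = *r* × φ(z_q) / (1 − *q*), where z_q is the *q*-quantile of the standard normal.

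- *q* = 0.10, *r* = 0.5: 0.5 × 0.1755 / 0.90 = 0.0975
- *q* = 0.20, *r* = 0.5: 0.5 × 0.2800 / 0.80 = 0.175
- *q* = 0.10, *r* = 0.3: 0.3 × 0.1755 / 0.90 = 0.0585

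Simulation gives:

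| Removed, massage / control | *r*, massage / control | Bias (SD) | Type I error |
|---|---|---|---|
| 10% / 10% | 0.5 / 0 | 0.09–0.10 | 9–10% |
| 20% / 10% | 0.5 / 0 | 0.17 | 20% |
| 10% / 10% | 0.3 / 0 | 0.06 | 7% |
| 10% / 10% | 0 / 0 | 0 | 5% |
| 10% / 10% | 0.5 / 0.5 | 0 | 5–6% |
| 10% / 10% | 0 / 0.5 | −0.09 | 10% |

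The last row reverses the roles of the arms. The bias then goes against massage.

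**5. Illustration with a response rate** (section 2.12 names a chi-square test)

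Assume a true response of 0.60 in both arms and 91 per arm. If a fraction *d* with response *s* is excluded, the retained response is (0.60 − *d* × *s*) / (1 − *d*). Excluded control children are taken to respond at 0.60, except in the last line.

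- 10% out of each arm, *s* = 0.30 in massage: (0.60 − 0.03) / 0.90 = 0.633. Spurious difference 3.3 points, type I error 0.07.
- 10% out of each arm, *s* = 0 in massage: 0.60 / 0.90 = 0.667. Difference 6.7 points, type I error 0.14.
- 15% out of massage with *s* = 0, 5% out of control: 0.60 / 0.85 = 0.706. Difference 10.6 points, type I error 0.29.
- 10% out of each arm, *s* = 0.30 in both: 0.633 in both. Difference 0, type I error 0.05.

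**The case against.** The best defence is that section 2.12 is the only place that sets the analysis population, and it is explicit. Section 2.3 concerns recruitment and never says that data will be discarded. Criterion 4 could be a misplaced withdrawal rule, and its English is rough: failing to complete the test might refer to baseline assessments, and inclusion criterion 5 reads naturally as willingness to cooperate. On this view a clarifying sentence would do.

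Part of this stands. Inclusion criterion 5 is weak evidence alone, and the text does not prove that sites or analysts will drop children. But nothing in the article says that section 2.12 prevails, and the clauses on treatment during the study and on incomplete efficacy data do not fit a screening reading. Site staff apply eligibility rules. A child declared ineligible may not be assessed again, and intention-to-treat cannot recover outcomes that were never collected. If a screening or withdrawal rule was meant, the wording still has to change.

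The criticisms of the magnitude also stand in part:

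- The larger figures need selection that differs by arm, and the direction of bias is not established.
- The 20% removal rate is twice the loss the protocol allows for.
- Sixty sessions is arithmetic, but sessions last 15 to 20 minutes, and the article does not say whether they need separate attendance. The extra burden on families is therefore an inference.
- Children who are truly lost have no week 12 outcome under either rule. Correcting criterion 4 helps only those whose outcomes could still be obtained.

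**Conclusion.** The concern holds. Criterion 4 and the primary analysis in section 2.12 give opposite instructions for any child who stops early, receives other influential treatment or has incomplete data. This is a conflict between two stated rules, not detail left to another document, and it decides who enters the primary comparison.

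The contradiction needs no assumption beyond the timing in section 2.4. The bias is possible, not certain. It is zero if removals are unrelated to outcome or match in number and prognosis across arms. Under the assumed selective removal in the massage arm, it ranges from about 0.06 to 0.17 SD, with type I error of 7 to 20%. On the response-rate scale it is about 3 to 11 points, with type I error of 7 to 29%. These figures are illustrative, not forecasts.

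**What to change.** 1. Limit exclusion criterion 4 to facts known before randomisation. Delete the clauses on non-completion, treatment during the study and incomplete data.
2. Reword inclusion criterion 5 as the family's stated willingness, at consent, to take part and attend assessments.
3. State in sections 2.10 and 2.12 that children who stop massage, miss sessions or start another treatment remain in follow-up where the family agrees, and are analysed in the group to which they were randomised. Record these events with their dates.
4. Use the deleted conditions only to define a secondary per-protocol set, fixed before the data are unblinded.
5. Section 4 reports that recruitment had begun and was continuing. List by arm any randomised child already removed under criterion 4, and obtain the remaining assessments where possible.

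The cost is a short amendment, a case report form instruction and some effort to keep in touch with families who stop treatment. No visits are added, because section 2.6.1 already schedules assessments at weeks 4, 8 and 12. The sample size of 182 does not change.
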